## **1- Outline the theoretical, empirical and/or conceptual basis, background evidence for the research proposal with relevant literature.**

The frequency, intensity and duration of heat waves are increasing globally (Bi et al. 2011), and with these increases we can expect with a high level of certainty a parallel rise in heat-related morbidity and mortality (Hajat, O'Connor & Kosatsky, 2010). In an attempt to combat this, there is a need for evidence-based guidelines to be made available that educate people on the steps they can take to protect themselves during extreme heat events. One particular population group at a disproportionately higher risk of morbidity and mortality during these extreme weather events is the elderly (Hajat, O'Connor & Kosatsky, 2010). Therefore, it is of great importance to make targeted recommendations for this population. Air-conditioning is the best protection during extreme heat events, but it is not accessible to many of the most vulnerable populations and widespread use and reliance on it during extreme heat events can cause blackouts (Kaiser et al., 2001; Semenza et al., 1996). Researchers began examining the effectiveness of using a fan as a cooling intervention and found that public health recommendations regarding fan-use were not uniform between agencies and often not evidence-based (Jay et al., 2015). If fan-use were to be found effective, it would provide a low-cost solution with a low-energy requirement. Research to date suggests that the benefits of fans have been greatly underestimated by public health agencies (Jay et al., 2015). Despite organizations such as the WHO, EPA and the Government of Victoria advising against using fans in hot conditions, a study published in the Journal of the American Medical Association (JAMA) demonstrated that fan use reduced physiological strain in young healthy men in simulated hot/humid heat wave conditions (Ravanelli et al., 2015). The use of a fan increased airflow which improved sweating efficiency and led to greater evaporative heat loss. The effectiveness of fan-use does depend on both the unique environmental conditions and the individual; it has been suggested that in certain conditions fans may be less effective and even harmful to older adults due to age-related decrements in sweating (Gagnon et al., 2016). Due to the findings to date it is clear that there is a need for evidence based recommendations specific to both the environmental conditions and population-specific, particularly those populations who have compromised thermoregulatory ability, such as the elderly. In a recent article by Jay and Capon (2017) it was proposed that external skin wetting could be used by the elderly to compensate for their decreased sweating ability, while still gaining the benefits of increased latent heat loss as a result of improved evaporative efficiency with fan-use. This combination has the potential to be a simple, cost-effective cooling intervention that has 50-times lower cost and electricity requirement than air conditioning and so therefore can be utilized by vulnerable populations in a low-resource environment. We propose the below study to examine if fan-use, in combination with skin-wetting can be an effective cooling strategy that is able to decrease the physiological strain experienced by elderly during heat waves, and as a result decrease their chance of experiencing an adverse cardiovascular event. During the 2003 heat wave in Lyon, France, antihypertensive use was associated with a 177% increased risk of mortality in adults presenting to the emergency department with heat stroke (Argaud et al., 2007). Due to this historical evidence and the prevalence of hypertension in older adults, it is important to include older adults on antihypertensives in our study to adequately represent the older adult population, while also investigating the impact of antihypertensive use on individuals' responses to simulated heat wave exposure and the proposed interventions. We believe the proposed project will provide evidence

that will help public health and government organizations make evidence-based environment and population specific recommendations for older adults during heatwaves.

## **2- Outline the methodology for the research proposal including:**

### *2.1. Research Questions:*

The primary research question guiding this project is: Are fans and/or skin wetting effective in decreasing the physiological strain experienced by elderly during a simulated hot humid heatwave (38°C with 60% relative humidity).

The secondary research question guiding this project is: are fans and/or skin-wetting effective in decreasing the physiological strain experienced by elderly during a simulated hot, dry heatwave (46°C with 10% relative humidity).

### *2.2 Research hypotheses:*

The research hypotheses for this study are:

1. In the hot and humid condition, all interventions will result in improved cooling compared to the control (no-fan) trial. With fan and skin-wetting (FSW) being the most effective, then no fan and skin-wetting (NFSW), then fan (F), and finally, the control, no-fan (NF).
2. In the very hot and dry condition, skin wetting with no fan (SWNF) will be the most effective cooling intervention followed by fan and skin-wetting (FSW). We expect the fan (F) intervention to be less effective than the control, no-fan (NF).

*2.3 Participant characteristics:* To complete this study, 56 (greater than or equal to 60 years) adults will be recruited from previous participants who have consented to being contacted for future studies and through the distribution of recruitment flyers at both the Cumberland and Camperdown campuses at The University of Sydney.

*2.4 Sample size:* The sample size computation is based on comparison of the primary endpoint (change in rate pressure product from baseline to the end of a 2 h simulated heatwave exposure to 38°C and 60% relative humidity) between the 4 conditions of control, fan use alone, skin wetting alone, fan use + skin wetting. This preliminary data from young healthy participants was provided by [name], a former PhD student from within our laboratory. A non-repeated measures ANOVA on this data demonstrates 20% (eta squared of 0.2) of the variability was due to the intervention. Using GPower 3.1.9.2 software, an ANCOVA: Fixed effects, main effects and interactions f-test was performed using an alpha of 0.05, beta of 0.1 and an effect size of 0.5 to determine a total sample size of 45 is needed to obtain sufficient statistical power. To account for approximately 20% loss to follow up, 56 participants will be included in the study. Of the 56 participants, 14 will be healthy older females, 14 will be healthy older males, 14 will be healthy females taking antihypertensive medication, and 14 will be older males taking antihypertensive medication.

### *2.5 Inclusion/Exclusion Criteria:*

Inclusion Criteria: Non-smokers or ex-smokers (greater than or equal to 1y since quitting), fluent/have no difficulty understanding and speaking English, and age of greater than or equal

to 60 y. Age will be matched across all groups. Participants with hypertension must have been diagnosed as hypertensive and taking antihypertensive medications.

Exclusion criteria: body mass index greater than or equal to 35. No history/signs/symptoms of coronary artery disease or heart failure. Currently undertaking hormone replacement therapy. Currently taking medications known to cause hyper- or hypo-hidrosis (except those taken for hypertension). Currently taking a beta-blocker. Evidence of current fluid and electrolyte disorders, anemia, abnormal thyroid function, arrhythmias, diabetes, renal disease, liver disease, cerebrovascular disease, significant pulmonary disease, endocrine abnormalities, uncontrolled hypertension (180/110mmHg), significant cognitive impairment, psychiatric disorder, substance abuse, degenerative neurological condition or any other medical condition deemed to pose risk during the proposed testing or experiments, or preclude them from completing the screening stress test.

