The notion that fan use may be detrimental in extremely hot conditions mostly likely arises from the understanding that as air temperature exceeds skin temperature (at  $\sim 35^{\circ}\text{C}$ ), more heat will flow into the body with additional air movement. After all, this is the basis upon which fan-assisted ovens accelerate cooking time. However, unlike a turkey in an oven, humans secrete sweat on to the skin surface when heated and the subsequent evaporative heat loss serves to greatly cool the body. Moreover, this evaporation is greatly enhanced with increased air velocity; leading to the evaporation of sweat that would otherwise sit on the skin, or drip off the body and provide no cooling. Therefore, it becomes clear that only when the additional heat gain with a fan cannot be counterbalanced by greater evaporative heat loss will fans accelerate body heating. Within this context, there are physiological limitations to sweating which will impact the efficacy of fan use. Age-related decrements in sweat output are progressively observed as early as 40 years of age, and while very little is known about sweating responses in individuals with coronary artery disease, the decreased ability to increase cardiac output sufficiently to maintain adequate levels of skin blood flow in CAD patients, particularly those prescribed cardio-selective beta-blockers, could further compromise heat dissipation.

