### *2.2 Research hypotheses:*

The research hypotheses for this study are:

3. In the hot and humid condition, all interventions will result in improved cooling compared to the control (no-fan) trial. With fan and skin-wetting (FSW) being the most effective, then no fan and skin-wetting (NFSW), then fan (F), and finally, the control, no-fan (NF).
4. In the very hot and dry condition, skin wetting with no fan (SWNF) will be the most effective cooling intervention followed by fan and skin-wetting (FSW). We expect the fan (F) intervention to be less effective than the control, no-fan (NF).

*4.3 Participant characteristics:* To complete this study, 56 (greater than or equal to 60 years) adults will be recruited from previous participants who have consented to being contacted for future studies and through the distribution of recruitment flyers at both the Cumberland and Camperdown campuses at The University of Sydney.

*4.4 Sample size:* The sample size computation is based on comparison of the primary endpoint (change in rate pressure product from baseline to the end of a 2 h simulated heatwave exposure to 38°C and 60% relative humidity) between the 4 conditions of control, fan use alone, skin wetting alone, fan use + skin wetting. This preliminary data from young healthy participants was provided by [name], a former PhD student from within our laboratory. A non-repeated measures ANOVA on this data demonstrates 20% (eta squared of 0.2) of the variability was due to the intervention. Using GPower 3.1.9.2 software, an ANCOVA: Fixed effects, main effects and interactions f-test was performed using an alpha of 0.05, beta of 0.1 and an effect size of 0.5 to determine a total sample size of 45 is needed to obtain sufficient statistical power. To account for approximately 20% loss to follow up, 56 participants will be included in the study. Of the 56 participants, 14 will be healthy older females, 14 will be healthy older males, 14 will be healthy females taking antihypertensive medication, and 14 will be older males taking antihypertensive medication.

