### 5.2 Description of the population

Participants will be male or female, aged between 50 and 80 years of age, with stable coronary artery disease.

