In Montreal, male or female participants aged between 50 and 80 years of age with stable coronary artery disease were to be included in the study. In Sydney, male or female participants aged 60 years or older were to be included in the study.

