### 5.2.3 Tertiary Analysis

To study the impact of beta-blockers on the effect of the cooling interventions, change in rate pressure product will be analyzed using a REML-based linear mixed model, accounting for repeated measures, including a term for condition (control, fan alone, skin wetting alone and fan + skin wetting), a term for beta-blockers (yes/no) and a term for the interaction between condition and beta-blockers. This interaction will be tested at the 0.10 significance level and will determine whether the condition effect is impacted by taking beta-blockers. Condition effects will be estimated and presented with 95% confidence interval within subgroup of beta-blockers (yes/no). This analysis will be conducted on the subset of subjects with coronary artery disease (CAD) under the 38°C and 60% RH heatwave exposure. The same analysis will also be conducted in the subset of subjects with CAD under the 45°C and 15% RH heatwave exposure, with condition being restricted to control and skin wetting.

Under each of the heatwave exposures separately, change from baseline in core temperature, whole-body sweat rate, thermal comfort and thermal sensation will be presented and analyzed as the primary endpoint using a REML-based linear mixed model, but 95% confidence intervals will be presented with the point estimates and comparisons will be tested at the 0.05 significance level.

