### 5.2.4 Other Subgroup Analysis

Subgroup analyses will be performed for the change in rate pressure product, looking at the homogeneity of the condition effect across the following factors: Sex (Female/ Male) and Site (Montreal/ Sydney).

The subgroup analyses will be conducted using a REML-based linear mixed model, accounting for repeated measures, including a term for condition, a term for the subgroup factor and the condition x subgroup factor interaction. This interaction will be tested at the 0.10 significance level and will determine whether the condition effect is impacted by the presence of the factor. Condition effects will be estimated and presented with 95% confidence interval within subgroups.

The subgroup analysis will be conducted separately under each of the heatwave exposures and will be considered exploratory.

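### The beta-blocker and site interaction tests (SAP 5.2.3, 5.2.4) compare non-randomised groups with no age term; an age-adjusted sensitivity version should be pre-specified

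*Supplement*

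**What the plan says.** The SAP pools the Sydney (2018-496) and Montreal (2019-2425) studies.

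- **SAP 5.2.3.** The beta-blocker model is fitted in CAD participants only. Besides condition it has "a term for beta-blockers (yes/no) and a term for the interaction between condition and beta-blockers".
- **SAP 5.2.4.** Homogeneity of the condition effect is examined across two factors, "Sex (Female/ Male) and Site (Montreal/ Sydney"). Each model has condition, the factor and their interaction. The analysis is labelled exploratory.
- **Decision rule.** Both interactions are tested at 0.10, and the SAP lets the result decide whether the factor affects the condition effect. SAP 5.2.5 does the same for season. No SAP model contains age, and age is not a subgroup factor.
- **Montreal population** (latest protocol, 5.2 and 6.1). Participants are "aged between 50 and 80 years of age, with stable coronary artery disease". The plan is for 17 on beta-blockers and 17 not, by existing prescription. No age matching is stated.
- **Sydney population** (SAP 2.1). "In Sydney, male or female participants aged 60 years or older were to be included in the study". No upper limit is given.
- **Sydney matching** (latest protocol, 4.5; the same sentence stands in 2.5 of the earlier version). "Age will be matched across all groups". The groups are the four cells of 14 in section 4.4, formed by sex and antihypertensive use.
- **Rationale** (Montreal protocol, section 2). "Age-related decrements in sweat output are progressively observed as early as 40 years of age". The same section concludes that a fan used alone can do harm in older people because they sweat less.

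**The concern.** The crossover protects contrasts between conditions within a person. It does not protect a comparison of that contrast between two sets of people. If the sets differ in age, and the cooling effect changes with age, the condition x group interaction contains an age component that the stated models cannot separate from the group effect.

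The plan itself names ageing as the reason why a fan may help or harm. It pre-specifies interactions with sex, site and season but not with age. The age criteria differ between sites at the lower end (50 against 60) and at the upper end (80 against none). The beta-blocker groups are formed by prescription, and whether a patient takes a beta-blocker may go with age. At stake are the answer to a stated tertiary objective (beta-blockers) and the reading of the site check.

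**Working it through.** **1. Inputs from the documents.** The SD of the between-condition difference is 2000 bpm x mmHg and the clinically relevant difference is 1250 (Montreal 6.1). Enrolment is 34 in Montreal, split 17/17 by beta-blocker use (Montreal 6.1), and 56 in Sydney (Sydney 4.4). The interaction tests are at 0.10 (SAP 5.2.3, 5.2.4).

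**2. The plan's own figures.** A paired t-test with difference 1250, SD 2000 and two-sided alpha 0.0167 has 80.5% power at n = 30, as stated. Then 30/0.90 = 33.3, so 34 are enrolled; 45/0.80 = 56.25, stated as 56. No stated figure is in dispute.

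**3. Inputs that are assumptions.** The documents give no age distribution and no slope. Ages spread evenly over the permitted range, with Sydney cut at 80, give means of 65 and 70, a gap of 5 years. I use gaps of 3 to 8 years and slopes of 250 to 750 bpm x mmHg per decade, with 500 as the central value.

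**4. Shift in one contrast.** Shift = gap x slope.
- Central: 5 x 50 = 250, which is 250/1250 = 20% of the clinically relevant difference.
- Range: 3 x 25 = 75 to 8 x 75 = 600.

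**5. Standard error of the group difference in one contrast.**
- Site: 2000 x sqrt(1/34 + 1/56) = 435.
- Beta-blockers: 2000 x sqrt(1/17 + 1/17) = 686.

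**6. Rejection rate of a single-contrast two-sided 0.10 test, with no true group effect beyond age.**

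| Comparison | Shift/SE, central | Rejection, central | Range |
|---|---|---|---|
| Site | 250/435 = 0.57 | about 16% | 10% to 40% |
| Beta-blockers | 250/686 = 0.36 | about 12% | 10% to 23% |

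The beta-blocker row holds only if the gap is systematic (see the objection).

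**7. Check on the full interaction test.** A simulation used four conditions, the 3-df interaction at 0.10, 2000 runs and an assumed within-group age SD of 6 years, with age acting equally on the three active conditions. At 5 years and 500 per decade the stated model rejected in 16.2% (site) and 11.9% (beta-blockers). With condition x age added, the rates were 11.2% and 10.7%, and the mean shift in a contrast fell from 258 to 9 (site) and from 241 to -12 (beta-blockers). With no age gap, the stated model rejected in about 10% and showed no bias.

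**8. Age as a main effect only.** Age is constant within a person and cancels from the contrast. With complete data the interaction estimate was unchanged (difference below 1e-10). The condition x age term is what matters.

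**9. Price in precision for site, under the age ranges of step 3.** Within-site age variance is 0.378 x 75 + 0.622 x 33.3 = 49.1. Between-site variance is 0.378 x 0.622 x 25 = 5.9. So r-squared = 5.9/55.0 = 0.107, variance inflation = 1/(1 - 0.107) = 1.12, and the SE widens by about 6%.

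**The case against.** Several objections stand and limit the point.

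- **Status.** The affected analyses are tertiary or exploratory. A reader might infer that the main result is biased by age. It is not: the primary and secondary comparisons with control are within-person.
- **Purpose of the site test.** SAP 5.2.4 presents it as a homogeneity check. If one site responds differently because its participants are older, that is real heterogeneity and not a false positive. The 16% counts as an error only if the result is attributed to something other than age. Sydney excludes CAD and Montreal requires it, so a reader might take site as a CAD comparison, but the SAP plans none. Site also differs in medication, wetting method (self-sponging against spraying), seat and visit order. Age adjustment cannot turn it into a CAD contrast.
- **Chance gaps.** A chance age difference between the beta-blocker groups averages zero and belongs to the between-person variation that sets the SE. It does not raise the unconditional 10% error rate. With ages even over 50 to 80, the SE of the mean age gap is sqrt(75 x 2/17) = 3.0 years, so a chance gap of 5 years or more has a probability of about 9%. Only a systematic gap biases the test, and no section shows one.
- **Sydney's matching.** A reader might infer that it was meant to balance these comparisons and fails to. It applies among Sydney's own groups and bears on neither.
- **Age floors.** A reader might infer that the Sydney sample is 10 years older. The criteria set a higher minimum; they do not give the sample's mean age.
- **Slope.** The reversal of the fan effect cited in the Montreal protocol compares ages 20-30 with 60-80 at 42°C. No slope within 50 to 80 at 38°C and 60% RH is given.

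What does not fall is the mechanism: the estimates absorb any age gap times any age slope, and the stated models leave no way to see how much.

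**Conclusion.** The concern holds as a minor point about exploratory analyses. The condition x beta-blocker and condition x site estimates come from non-randomised groups, with no adjustment for the one characteristic that the plan's rationale names as changing the effect of a fan. The size is unknown. The central illustration (shift 250; site rejection about 16% instead of 10%) rests on an assumed systematic gap of 5 years and an assumed slope of 500 bpm x mmHg per decade. If either is zero, there is no bias. The documents do not support a claim that a spurious CAD or beta-blocker effect will be reported, only that the stated models could not tell one from an age effect.

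**What to change.** Keep the models in SAP 5.2.3 and 5.2.4 as written, and add a pre-specified sensitivity version of each.

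1. Include age at enrolment (continuous, centred) **and** condition x age.
2. Report the beta-blocker and site interactions with and without this adjustment.
3. Report the condition x age slope with its 95% confidence interval, labelled exploratory.
4. State that the site interaction, even when age-adjusted, is a homogeneity check and not an estimate of a CAD effect, because site also differs in CAD status, medication, wetting method, seat and visit order.

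The cost is SAP wording; age is already needed for eligibility. At 38°C and 60% RH each model gains four fixed-effect parameters (one for age, three for condition x age). The SE of the site interaction widens by about 6% under the even age ranges. The loss grows if groups differ in age and ages within a group are less spread: in the simulation with a 5-year gap at 500 per decade, the SD of the estimate rose from 446 to 487 for site (9%) and from 702 to 776 for beta-blockers (11%). Keeping the unadjusted models alongside means that nothing is given up.

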## 2.6 *Data collection protocol:*

The 2 preliminary sessions and the 4 experimental sessions (with the option of doing an additional 4 experimental trials) will take place at the University of Sydney, Cumberland Campus. The time involvement will be approximately 2 hours for the first preliminary session, 1 hour for the second preliminary session and 3 hours for each of the experimental sessions. This involves a total time commitment of approximately 15 hours (or approximately 27 hours if the participant chooses to do an additional four trials). We are recruiting participants for at least four experimental sessions that will take place in the hot, humid condition and providing them with the option of doing an additional four experimental sessions that will be carried out under a different simulated heatwave condition (very hot, dry). These two simulated heatwaves provide very different interactions between the individual, the environment and the proposed interventions and so it is of great importance to study both types. For example, in a previous study carried out in our lab a fan was beneficial in hot-humid conditions due to the increased airflow increasing sweating efficiency and therefore evaporative heat loss, whereas in the hot-dry condition the increased airflow accelerated dry heat gain and so fan-use was actually unfavourable. We understand that the two preliminary sessions and 8 experimental sessions are a big time commitment and so we have chosen to take the above approach to minimize attrition for the primary objective. Investigating the low cost at-home cooling interventions in the hot, humid condition is our primary objective as these are the types of heatwaves most common worldwide. Investigating the same interventions in the very hot, dry condition allows us to investigate their impact in the type of heatwave most prevalent in Australia.

*Pre-screening and preliminary sessions:* Participants will be initially screened over the phone using a standardized phone screen based on the inclusion and exclusion criteria of our study. If the participants pass the phone screen they will be invited in for a preliminary session. The first preliminary session involves a complete medical history, physical examination and cardiac stress test. This screening will be carried out by geriatrician [name]. During the second preliminary session the participant will be asked to arrive fasted and their body composition will be determined and a full blood count will be taken. These preliminary sessions are important to further determine their eligibility for the study and deem them safe to participate. The following equipment and techniques will be used:

- Body Composition:** Body composition will be determined using dual x-ray absorptiometry, which is an enhanced form of x-ray technology that will assess the distribution of muscle, fat, water and bone within their body.
- Cardiac Stress Test:** The participant will undergo a physician-supervised graded exercise test on a treadmill while undergoing ECG and blood pressure monitoring. Both are described below.
- Venepuncture:** A blood sample will be obtained by peripheral puncture of the forearm vein during their second preliminary session. Venepuncture will be performed by personnel with phlebotomy training.

If the participant agrees to participate in this study, they will undergo testing at the Cumberland Campus of the University of Sydney for approximately three hours on 4 separate occasions. (There is an option to participate in an additional four experimental sessions.) Each experimental session will be separated by at least 72 hours. Participants will be asked to abstain from alcohol and caffeine, avoid strenuous exercise in the 12 h prior to each experimental session, and will be instructed to consume a light meal and 0.5L of water ~2 h before arriving at the lab. They will be provided with a standardized singlet and shorts to wear and will undergo 30-min of baseline rest (seated) in a thermoneutral room (~24°C), where they will be instrumented using the equipment described below. After 30-min, they will then enter a climate-controlled chamber, where they will be seated unrestrained in a standard armchair for the remainder of the 2-hour experimental protocol. This protocol will consist of the participant sitting in a 38°C and 60% relative humidity room. (If they choose to participate in the additional four trials the conditions will be 46°C and 10% relative humidity). During each session the participant will undergo one of the following four conditions: no cooling intervention, use of an electric fan, self-wetting the skin with a sponge, or use of an electric fan while self-wetting the skin with a sponge. Additionally, in all trials they will be asked to drink 250 ml of cold (~18°C) water every half-hour (750 ml total). In all fan trials, they will be seated 1.0 m from an 18" diameter fan set to the highest setting. The following equipment and techniques will be used:

- Rectal temperature sensor:** The participant will be asked to insert a flexible sensor 10-12cm into their rectum. A marker is placed on the sensor using sterile surgical tape. The participant will insert the sensor until the tape reaches their anal surface. The insertion of the sensor may cause some mild discomfort and minor irritation; however, this sensation soon passes. The participant will receive proper instruction regarding the placement of the sensor to ensure their safety and comfort. The participant will be responsible for the insertion of this sensor. It will provide the researcher with an indication of the amount of heat stored in their body and will be tracked throughout the entirety of each experimental session
- Skin temperature sensors:** Eight skin sensors will be taped to the participants skin surface with hypoallergenic tape. Some hair may need to be shaved (by the use of disposable razors) in order to secure the probes adequately. These probes give an indication of skin temperature and heat loss from the skin and will be recorded throughout the entirety of each experimental session.
- Blood pressure:** An automated blood pressure monitor will be strapped to the participants arm and blood pressure will be taken every fifteen minutes during the experimental protocol and will be used by researchers to better characterize skin and limb blood flow and calculate RPP

(heart rate x systolic blood pressure). Blood pressure will also be taken three times during the orthostatic intolerance test described below.

- ECG monitoring: 12 soft electrodes will be stuck to the participants torso and will measure the electrical signals of their heart. This will produce signals on a display that will be continuously monitored to ensure the participants safety throughout the cardiac stress test during the first preliminary session and each experimental session.

- Heart rate: Heart rate will be measured using the ECG monitoring.

- Skin blood flow: A flexible laser probe will measure skin blood flow non-invasively at the upper back during the entirety of each experimental session. This measurement device does not result in any discomfort or residual medical effects.

- Limb blood flow: Limb blood flow will be determined using venous occlusion plethysmography. This technique involves a rapidly inflating cuff around the participants arm to a pressure of ~60 mmHg (compared to ~180 mmHg during a blood pressure reading). A strain gauge that resembles an elastic band will be placed on their forearm and this will record minor changes in limb volume. This measurement will be taken every thirty minutes during each experimental session.

- Ventilated sweat capsules: A small plastic capsule connected to plastic tubing will be placed on the participants upper back and forearm. Dry air is passed through this capsule and a humidity sensor will pick up humidity from the skin and provides a measurement of local sweat rate throughout each experimental session.

- Cognitive test: The participant will be asked to complete a short-form of the Stroop Colour and Word Test (SCWT) immediately before and at the completion of the heatwave exposure. This test involves them looking at various words and identifying which color the words are shown in.

- Whole-body sweat loss: The participant will be weighed on a platform scale immediately before and at the completion of the heatwave exposure in order to compare whole-body sweat losses.

- Rating of thermal comfort and sensation: The participant will be asked to rate how warm they feel and how uncomfortable the heat makes them on two separate visual analogue scales every fifteen minutes during each experimental session.

- Nausea and lightheadedness scale: The participant will be asked to rate how much (if any) nausea or lightheadedness they are experiencing and tick if they are experiencing any other symptoms (including paleness, muscle cramps, tiredness, weakness and headache) every fifteen minutes during each experimental session.

- Orthostatic hypotension: At the completion of the heatwave exposure the participants blood pressure will be taken. They will then be asked to stand up and their blood pressure will be taken after 1 minute of standing and then again after 3 minutes of standing. This test is carried

out to see if there is evidence of postural hypotension (a drop in blood pressure within 3 minutes of standing from a seated position).

All equipment and procedures described above are commonly used procedures and have been used multiple times by the investigators conducting the study (1-4, 9, 10) as well as research groups (5-8) in the field of thermoregulation across the world and these methods are all in accordance with the Declaration of Helsinki.

